#### Health care Utilization

Asthma-related ED visits or hospitalizations will be abstracted from provincial database (RAMQ) using validated algorithms [134] which lists information on the date, type, provider, and location of service delivery (e.g. inpatient, emergency, clinic) for all medical services remunerated on a fee-for-service basis (approximately 86% of all services) [135].

Resource Utilization: "Information on the time spent by the nurse case manager (type of call, who is making the call, duration and reason) will be recorded, and will allow us to address health service research issues and knowledge translation to other practitioners and health care organizations. All health-care resources used during the 6-month follow-up will be considered. Intervention costs will include resources used to develop the web-based tool, train patients and nurses to use the system, administer the intervention (time spent for research data collection will not be included). Real time spent with each patient will be carefully documented by each study case manager. Case manager salary costs will be estimated based on the average pay scale of the Federation of Nurses of Quebec. Physician fees will be based on those set by the Provincial Health Insurance Board [136]. "Healthcare utilisation": Information from the provincial health insurance program administrator, RAMQ, will be obtained on asthma-related ER visits or hospitalizations. Total cost per ED visit will be based on data from earlier studies conducted in the province of Quebec [137,138]. ED visit will be a separate resource item from hospitalization. Hospitalization costs will be based on a Quebec index called the Niveau d'Intensité Relatif des Ressources Utilisées (NIRRU)" [139].

### Sample Size

The primary outcome for this study is change in asthma control. We hypothesized that use of MAP would be associated with a 10% reduction in the proportion of patients classified as being in poor control. Based on MOXXI-II results, we have estimated that 19% of asthma patients will either be seen in the ED for respiratory-related problems, or use greater than 500 doses of fast-acting beta2-agonists in a 6-month period. Thus the intervention would need to reduce the proportion of asthmatics in poor control to 9% to be considered to be sufficiently effective for policy and practice adoption.

Thus, to detect a 10% difference in proportions, [140] with 80% power using a cutoff for statistical significance of 0.05, the sample size needed is 67 participants in total. To account for attrition and loss to follow-up, we will recruit an additional 13 subjects for a total of 80 participants, and 40 participants per arm [141].

This sample size will also allow us to detect a minimal important difference of .5 on the AQLQ [113,142], using the Mini-AQLQ a difference as large as 0.97 (SD .61) was found to be clinically meaningful and significant [114,143-145].

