### Inclusion criteria

a) Males and females Age 18 to 69 years

b) Physician diagnosis of asthma and prescribed at least one rescue medication.

c) Classified as having poor asthma control by their doctor

d) Access to the internet

e) Smoking < 20 pack-years

f) Can speak and understand English or French

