### Primary Outcomes

**Asthma control **will be evaluated by examining overuse of rescue fast acting bronchodilators (beta2-agonists) (FABA) (i.e. participants will be classified as overused yes/no). Excessive use of rescue fast acting bronchodilators was included as an indicator because it is associated with an increased risk of hospitalization and death from asthma [110], and is defined as the dispensing of more than 500 doses of the most commonly prescribed fast acting beta2-agonist salbutamol 100 mcg, 2 inhalations at the time, or the equivalent for other fast acting bronchodilators in the last six months of follow-up. Doses dispensed will be based on quantities recorded in dispensed prescriptions from the RAMQ and private pharmacy prescription files. The maximum acceptable use of fast acting beta2-agonists is derived from recommendations in the guidelines that allow up to 3 doses per week and a daily dose for the prevention of exercise induced symptoms [51]. Previously developed methods will be used to adjust quantities dispensed for prescriptions filled before and immediately before the end of the item window for assessment [111].

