#### Statistical methods

Descriptive statistics will be used to evaluate differences in the baseline characteristics of participating patients in the two arms of the trial. Study hypotheses will be tested using an intention-to-treat analysis, whereby all consenting patients who were randomized during the accrual period will be included in the analysis. Analysis of the primary outcome, the proportion in each group that are in control and out of control based on doses of fast-acting beta2-agonists, will be compared using a chi-square test. Changes on the Mini-Asthma Quality of Life Questionnaire (AQLQ) will be compared by independent sample t -tests, and differences between mean change scores will be expressed with 95% confidence intervals (CIs). To deal with missing data we will conduct a sensitivity analysis using multiple imputation [146,147] to explore the effects of missing data on the results. Changes in other secondary outcomes, including COPD HRQL, will be evaluated using t-tests for continuous variables and chi-square for categorical variables [141], such as individual items on the TAM that asked about perceived benefit of features of the system and intention to use the system. While our sample size will limit our ability to conduct extensive multivariate analyses, we will assess which characteristics are associated with changes in the primary outcome using multivariate regression analyses with selecting variables in each model and adjusting for potential effect modifiers, (e.g. self-efficacy, adherence, age, sex).

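### The 19% planning rate and 9% adoption benchmark belong to an ED-visit-or-overuse composite in asthma patients generally, not to the overuse-only primary outcome in poorly controlled patients

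*Protocol article*

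**What the plan says.** All references are to the protocol article.

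- **Sample Size.** The control rate is 19%, estimated from MOXXI-II for asthma patients who would "either be seen in the ED for respiratory-related problems, or use greater than 500 doses of fast-acting beta2-agonists in a 6-month period". The hypothesised benefit is a 10-point reduction. The resulting 9% is described as the level the intervention must reach to merit uptake in policy and practice. The stated need is 67 patients in total for 80% power at 0.05, raised to 80 (40 per arm) for attrition.
- **Primary Outcomes.** Asthma control is assessed by "examining overuse of rescue fast acting bronchodilators (beta2-agonists) (FABA) (i.e. participants will be classified as overused yes/no"). Overuse is "defined as the dispensing of more than 500 doses of the most commonly prescribed fast acting beta2-agonist salbutamol 100 mcg" or equivalent, over the last six months of follow-up. ED visits play no part.
- **Statistical methods.** The comparison follows that definition: "the proportion in each group that are in control and out of control based on doses of fast-acting beta2-agonists, will be compared using a chi-square".
- **Inclusion criteria.** Patients must be "Classified as having poor asthma control by their doctor". The Participants section adds that they come from pulmonary clinics in two tertiary hospitals.
- **Health care Utilization** (under Secondary Outcomes). "Asthma-related ED visits or hospitalizations will be abstracted from provincial database (RAMQ"). This is the only place where ED visits enter as an outcome.

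**The concern.** The planning rate and the analysed outcome differ in two ways. The planning rate counts a patient as poorly controlled for an ED visit or for overuse, whereas the analysis counts overuse only. The planning rate is also stated for asthma patients without any restriction, whereas the trial enrols patients already judged poorly controlled. Nothing in the article converts one into the other.

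Two things are at stake. First, the stated 80% power rests on a rate that is not a rate of the tested outcome. Second, the 9% benchmark was set on the composite, but the trial will report overuse. An observed 9% overuse rate could coexist with a higher composite rate and still be read as meeting the benchmark.

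**Working it through.** **Step 1. Compare the definitions.**

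| | Sample Size | Primary Outcomes and Statistical methods |
|---|---|---|
| Event | ED visit or more than 500 doses | More than 500 doses |
| Window | 6 months | Last six months of follow-up |
| Population | Asthma patients (MOXXI-II) | Patients rated poorly controlled by their doctor |

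Threshold and window length agree. The endpoint difference is exactly the ED component.

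**Step 2. Direction of the error.** In one population, P(overuse) ≤ P(ED visit or overuse), so dropping the ED component can only lower the rate or leave it unchanged. Selecting poorly controlled patients plausibly raises it. The article gives neither an overuse-only rate nor a rate in poorly controlled patients, so the net direction cannot be determined.

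**Step 3. Try to reproduce the plan's own figure.** Inputs: p1 = 0.19, p2 = 0.09, 1:1 allocation, power 0.80, two-sided 0.05 (the article does not state sidedness). Pooled-variance formula, with p̄ = (p1 + p2)/2 = 0.14:

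n per arm = [1.960·√(2·p̄(1 − p̄)) + 0.842·√(p1(1 − p1) + p2(1 − p2))]² / (p1 − p2)²

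= (0.962 + 0.409)² / 0.01 = 187.8, so 188 per arm, 376 in total.

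A one-sided test gives 148 per arm, 296 in total. Neither is near 67. Power from the same approximation is

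Φ{[(p1 − p2)·√n − 1.960·√(2·p̄(1 − p̄))] / √(p1(1 − p1) + p2(1 − p2))}

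with n per arm. For 19% vs 9% it is Φ(−0.789) = 0.22 at 33.5 per arm (67 in total) and Φ(−0.678) = 0.25 at 40 per arm (80 in total).

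**Step 4. Power under assumed overuse-only rates.** The control rates below are assumptions, chosen on both sides of 19% because the direction is unknown. Each is paired with the plan's absolute reduction (10 points) and with its implied relative one (intervention rate = 9/19 of the control rate). Two-sided 0.05.

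| Control rate (assumed) | Reduction | Intervention rate | Power, 67 in total | Power, 80 in total |
|---|---|---|---|---|
| 12% | 10 points | 2% | 0.36 | 0.42 |
| 12% | 9/19 | 5.7% | 0.15 | 0.17 |
| 15% | 10 points | 5% | 0.27 | 0.32 |
| 15% | 9/19 | 7.1% | 0.17 | 0.20 |
| 19% (as stated) | both coincide | 9% | 0.22 | 0.25 |
| 30% | 10 points | 20% | 0.15 | 0.18 |
| 30% | 9/19 | 14.2% | 0.34 | 0.40 |
| 50% | 10 points | 40% | 0.13 | 0.14 |
| 50% | 9/19 | 23.7% | 0.61 | 0.69 |
| 60% | 10 points | 50% | 0.13 | 0.14 |
| 60% | 9/19 | 28.4% | 0.75 | 0.82 |

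Below 19%, the absolute reduction gives more power than 19% vs 9% and the relative reduction gives less. Above 19% the order reverses. The lowest rates are the roughest: 12% vs 2% implies only 40 × (0.12 + 0.02) = 5.6 expected events in 80 patients, where the normal approximation is poor.

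**The case against.** **Overuse is the settled endpoint.** The abstract, Primary Outcomes and Statistical methods all rest control on dispensed rescue medication; only the sample-size paragraph departs from this. That stands, and it means the paragraph to correct is the sample-size one. A reader might infer that the primary outcome should be changed to the composite. The documents do not call for that: it would replace the primary endpoint of an ongoing trial, bring in incompletely captured ED visits, and still leave 19% as a rate for asthma patients in general.

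**The low power has another cause.** A reader might infer that the mismatch is why the trial is underpowered. It is not. With 19% and 9% taken at face value, power is already about 0.22 to 0.25, because 67 does not follow from the stated inputs. That is a separate defect.

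**The population gap rests on thin text.** The article describes MOXXI-II only as asthma patients, and that cohort may itself have been selected. This stands as a limit, so the population argument is secondary. The endpoint mismatch does not depend on it.

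**The 9% is a rationale in a pilot.** No analysis applies it as a decision rule, and the Discussion foresees further studies if benefit is found. That is fair: it should not be called a formal success criterion. But the article does tie it to adoption, so readers can be expected to compare results with it.

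**Conclusion.** The mismatch is real and is stated in the text. The 19% and 9% are composite figures for asthma patients, used as if they were overuse rates in poorly controlled patients. They are unsupported for the analysed outcome, and the article does not allow the error to be signed or sized. A claim that power is simply lower than planned because of the mismatch would need one particular choice of effect scale on each side of 19%. Across both scales, power with 80 patients runs from 0.14 to 0.82, against 0.25 for 19% vs 9%.

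These powers assume the tabulated control rates, a two-sided 0.05 test, equal arms and a normal approximation. The endpoint mismatch itself needs none of these assumptions.

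**What to change.** 1. Keep overuse as the primary outcome.
2. In Sample Size, remove 19% and 9% as its planning rate and adoption benchmark, or label them as composite figures from MOXXI-II.
3. Restate power at 67 and 80 patients over a stated range of overuse-only rates in poorly controlled patients, for both absolute and relative reductions. State the sidedness. The non-reproducing 67 must be dealt with in the same revision.
4. Add the ED-or-overuse composite as a secondary outcome, with its components shown separately, so that any comparison with 9% uses the endpoint on which it was set. Choose one ED definition: Sample Size says respiratory-related, Health care Utilization says asthma-related.
5. Settle this before outcome data are examined.

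The cost is a rewritten paragraph and one derived variable, since ED visits are already drawn from RAMQ. The downsides are small. The stated power will look less favourable, and the ED component will be limited to fee-for-service billing, about 86% of services.

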**Methods:**

The trial is a parallel multi-centered 2-arm pilot randomized controlled trial. Participants are randomly assigned to one of two conditions: a) MAP and usual care; or b) usual care alone. Individuals will be included if they are between 18 and 70, have a confirmed asthma diagnosis, and their asthma is classified as not well controlled by their physician. Asthma control will be evaluated by calculating the amount of fast acting beta agonists recorded as dispensed in the provincial drug database, and asthma quality of life using the Mini Asthma Related Quality of Life Questionnaire. Power calculations indicated a needed total sample size of 80 subjects. Data are collected at baseline, 3, 6, and 9 months post randomization. Recruitment started in March 2010 and the inclusion of patients in the trial in June 2010.

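### 67 participants give about 21% power, not 80%, for 19% versus 9% in poor control; about 376 analysed would be needed

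*Protocol article*

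**What the plan says.** The Sample Size section gives nearly every input. For the control rate, "we have estimated that 19% of asthma patients will either be seen in the ED for respiratory-related problems" or exceed 500 doses of fast-acting beta2-agonist in six months. For the target, MAP must "reduce the proportion of asthmatics in poor control to 9% to be considered to be sufficiently effective for policy and practice adoption". The calculation is made "to detect a 10% difference in proportions", and the result is that "with 80% power using a cutoff for statistical significance of 0.05, the sample size needed is 67 participants in total". Thirteen more are added for attrition, giving 80, or 40 per arm.

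Under Statistical methods, the proportions in and out of control in each group "will be compared using a chi-square test". The Abstract (Methods) repeats the outcome without qualification: "Power calculations indicated a needed total sample size of 80 subjects". Whether the test is one- or two-sided is not stated.

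**The concern.** A 10-point difference between two independent proportions, with the higher one near 20%, normally needs well over a hundred patients per arm. With 67 in total there are about 33.5 per arm, so the expected counts in poor control are about 6.4 (0.19 × 33.5) against 3.0 (0.09 × 33.5). A gap of about three events cannot carry 80% power.

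The 67 is the only sample size the article derives, and it is tied to an effect described as large enough for policy and practice adoption. If the true power is about one in five, a non-significant result is the likely outcome even when the hypothesis is exactly right. A reader who trusts the 80% could read that result as lack of efficacy.

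**Working it through.** **Inputs.** From Sample Size: p1 = 0.19, p2 = 0.09, difference d = 0.10, significance level 0.05, power 0.80, 1:1 allocation, 67 in total before attrition and 80 after. From Statistical methods: a between-arm chi-square test. Assumption: two-sided, the usual reading of a chi-square test; one-sided results are given alongside.

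**Sample size, pooled-variance formula.**

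n per arm = [z(α)·√(2·p̄·(1−p̄)) + z(β)·√(p1(1−p1) + p2(1−p2))]² / d²

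- p̄ = 0.14, so √(2 × 0.14 × 0.86) = √0.2408 = 0.4907
- √(0.1539 + 0.0819) = √0.2358 = 0.4856
- Two-sided: (1.960 × 0.4907 + 0.8416 × 0.4856)² / 0.01 = (0.9618 + 0.4087)² / 0.01 = 187.8, so 188 per arm and 376 in total
- One-sided: (1.645 × 0.4907 + 0.4087)² / 0.01 = 147.8, so 148 per arm and 296 in total

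**Attempts to reproduce 67.**

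| Version | Total, two-sided | Total, one-sided |
|---|---|---|
| Pooled variance | 376 | 296 |
| Continuity-corrected | 416 | 336 |
| Unpooled variance | 372 | 292 |
| Arcsine | 368 | 290 |
| 10% read as a relative reduction (19% to 17.1%) | 12,862 | 10,132 |

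None is near 67. The closest number found is 64.3, from a one-sample formula that uses only the variance at 9%: (1.960 + 0.8416)² × 0.0819 / 0.01. It leaves out the control arm, so it does not describe the planned comparison.

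**Power at the stated sizes.** Power = Φ[(d·√n − z(α) × 0.4907) / 0.4856]

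- n = 33.5 per arm, two-sided: (0.5788 − 0.9618) / 0.4856 = −0.789, power 21.5%; one-sided 31.9%
- n = 40 per arm, two-sided: (0.6325 − 0.9618) / 0.4856 = −0.678, power 24.9%; one-sided 36.0%
- 67 read as per arm: 38.4% two-sided, 50.9% one-sided
- n = 188 per arm, two-sided: 80.0%

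**Exact check.** Enumerating all binomial outcomes for the uncorrected Pearson chi-square at two-sided 0.05 gives 21.3% with 34 control and 33 MAP patients, 26.1% with 40 per arm and 80.7% with 188 per arm. Fisher's exact test gives 13.1% for 34/33 and 16.7% for 40/40.

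**What these sizes could detect.** By the normal approximation, 67 analysed never reaches 80% power from a 19% control rate: power is about 77% even when the MAP rate is almost zero. With 80 analysed, the MAP rate would have to be about 0.6% or lower. By exact chi-square enumeration the corresponding rates are about 0.8% (67 analysed) and 2.0% (80 analysed). By either method, poor control would have to all but disappear in the MAP arm.

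**Precision.** Expected 95% half-width for the risk difference = 1.96 × √(0.2358 / n): 0.164 at 33.5 per arm and 0.150 at 40 per arm. Both are wider than the 10-point target.

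**The case against.** The strongest defence is that this is called a pilot, and a pilot need not be powered for efficacy. That is true in general. Here, however, the article makes an explicit 80% power claim for a named difference, and its Objectives section says efficacy will be tested. The label does not make the number correct.

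Other points deserve a fair hearing:

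- **Unseen source and sidedness.** The reference cited for the calculation is not available and sidedness is not stated. All other inputs are printed, and a one-sided test does not rescue the figure.
- **Paired reading.** The primary outcome is described as a change in asthma control, which might suggest a within-patient calculation. Statistical methods fixes a between-group chi-square.
- **Mini-AQLQ.** It is also listed under Primary Outcomes. If the printed SD of 0.61 applies to the 0.5 difference, 48 in total suffice for it. That depends on the SD: 72 would be needed at 0.75 and 126 at 1.0. This limits the error to the binary outcome but does not repair it, because the 67 is derived from the binary outcome.
- **Composite rate.** The 19% covers ED visits or overuse, while the analysed outcome is overuse alone. That is a separate matter; it means the corrected power statement should be conditional on the 19%.
- **Misreading.** The article does not say how a null result will be interpreted. Misreading is a risk, not a certainty.

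**Conclusion.** The statement is wrong as written. For 19% against 9%, compared between two equal arms by chi-square at two-sided 0.05, 80% power needs 188 per arm, 376 analysed in total. With 67 analysed the power is about 21%, and with all 80 it is about 25% (26% by exact enumeration). If the hypothesis is exactly true, the test of asthma control would miss significance about 75% to 79% of the time by the normal approximation.

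The conclusion rests on the article's own rates and on the two-sided reading. It survives a one-sided test (296 needed, about 32% power at 67) and survives reading 67 as a per-arm number. It concerns the binary asthma-control outcome only.

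**What to change.** Keep 80 participants and replace the power claim in Sample Size with wording such as: *If 19% of control patients are in poor control, the trial has about 21% power (67 analysed) to 25% power (80 analysed) to detect a reduction to 9% with a two-sided chi-square test at 0.05; 188 analysed per arm would be needed for 80% power.* State the sidedness. Change the Abstract sentence so that it no longer presents 80 as the result of a power calculation for this outcome.

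Two additions are advisable but not needed to correct the error. First, report the risk difference with its 95% confidence interval (expected half-width about 15 to 16 points) as the main result for this outcome. Second, say that a non-significant test is not evidence of no effect, and that this pilot alone will not settle policy adoption.

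The cost is wording in two places and a less favourable stated power, with no extra patients. Powering the trial for this difference instead would mean recruiting about 449, using the article's own attrition allowance: 13/80 = 16.25%, and 376 / (1 − 0.1625) = 449.

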### Recruitment

Potential participants are informed about the trial by their respirologist or the nursing staff. For individuals who agree to participate, the research coordinator further describes the study, responds to questions, and obtains informed and written consent.

### Study Procedure

#### Randomization

Treatment allocation is done by random permutation within blocks with block sizes of 4 and 6. Randomization is stratified by center. The randomization is done independently of centres, coordinator, and clinical staff. The randomization is performed with a randomization algorithm developed as part of the McGill University clinical and health informatics research tool kit. The relevant information is only accessible to an employee of McGill University Health Center who is not involved in the trial. After the inclusion of a participant in the trial and the baseline assessment, the study coordinator receives information concerning the allocation of patients to the intervention or control arm by sequentially generated logs through the study coordinator online system. Therefore, the fidelity of allocation is guaranteed.

